## Abstract

**Background:**

Parents’ mental illness (MI) and parental history of early life maltreatment (ELM) are known to be significant risk factors for poor parenting while poor parenting is a crucial mediator of the intergenerational continuity of child maltreatment. Hence, maltreatment prevention programs for families with an MI parent, which pay particular attention to experiences of ELM in the parent, are urgently needed. Parental mentalizing was previously found to mediate successful parenting. Interventions aimed at improving the parental mentalizing capacity reduced maltreatment risk in parents. The aim of the present study is to investigate the effectiveness of a mentalization-based parenting-counseling in acutely mentally ill parents currently treated at a psychiatric hospital.

**Methods:**

Mentalization-based parenting-counseling (MB-PC) vs. enhanced standard clinical care (SCC+) will be administered in a cluster-randomized-controlled trial (RCT). Patients treated at psychiatric hospitals with children between 1.5 and 15 years will be included in the trial. MB-PC will be administered as a 12-h combined individual and group program enriched by social counseling (over a course of 5 weeks) as add-on to standard clinical care, while the control condition will be standard clinical care plus a 90-min psychoeducation workshop on positive parenting. Primary efficacy endpoint is self-reported parenting practices at follow-up. Embedded within the RCT will be two sub-studies investigating social cognition and dyadic synchrony as biobehavioral mechanisms of change.

**Discussion:**

The main goal of the present study is to investigate ways to break the intergenerational continuity of maltreatment by assessing the benefits of a prevention program which aims at improving parenting in vulnerable mothers and fathers. MB-PC is a short, low-cost intervention which can be delivered by nurses and social workers and is applicable to MI patients with children with a broad range of diagnoses. If it is shown to be effective, it can be directly implemented into standard psychiatric hospital care thereby providing help to prevent child maltreatment.

**Trial registration:**

German Clinical Trials Register DRKS00017398. Registered on 5 July 2019

## Administrative information

Note: the numbers in curly brackets in this protocol refer to SPIRIT checklist item numbers. The order of the items has been modified to group similar items (see http://www.equator-network.org/reporting-guidelines/spirit-2013-statement-defining-standard-protocol-items-for-clinical-trials/).

## Introduction

### Background and rationale {6a}

Poor parenting is a crucial mediator of the intergenerational continuity of child maltreatment. Parents’ mental illness (MI) and parental history of early life maltreatment (ELM) are known to be the most significant risk factors in this vicious cycle of abuse: MI and a history of ELM are both associated with child abuse potential [1]. Ten years ago a guidance of the World Psychiatric Association (WPA) has been dedicated to the protection and promotion of mental health in children of persons with severe mental disorders indicating that not the diagnosis but severity and chronicity of psychopathology confer an increased risk for child maltreatment [2]. Furthermore, it has been shown that ELM alone does not significantly impact on parenting behavior but that mothers with a history of MI and severe ELM show a particularly high risk of low maternal sensitivity in interaction with their children [3, 4]. About 3.8 million minors in Germany live in families with an MI parent [5]. In a nationwide survey of mental health professionals at psychiatric hospitals in Germany, 38.3% of the surveyed evaluated their patients as being impaired in parenting, at least sometimes, and 52.3% of the surveyed estimated the mental health of their patients’ children to be jeopardized [6]. Furthermore, MI parents often consider their children as having more psychological/behavioral problems and express a higher need for help in parenting than a healthy control group [5]. It is important to note that investigations of parenting report statistical associations in large samples. Many parents with severe mental illnesses show excellent caregiving that means a parental MI or experience of ELM do not necessarily lead to poor parenting and it is not inevitable that there is a negative impact on the children’s development. Nevertheless, children living in a family with an MI parent run a higher risk of being affected by various modes of ELM [7] and of developing psychopathology [8]. Although studies on parent-child-interaction and maltreatment of minors have been widely restricted to mothers, it has also been shown that ELM in fathers predicts harsh parenting [9] and parental neglect [10]. Additionally, MI such as depression in fathers is associated with, e.g., more withdrawn parental behavior [11] and increased risk of child maltreatment [12]. Hence, prevention programs for families with an MI parent, which pay particular attention to experiences of ELM in the parent, are urgently needed.

The Guidelines of the World Psychiatric Association (WPA) outline impaired responsiveness to the child’s needs, emotional unavailability, irritability, and disturbed behaviors as common pathways through which MI in parents, irrespective of the specific diagnosis, impact on their child’s well-being [2]. These pathways interact strongly with poor mentalizing, which has been shown to be a significant mediator of poor parenting and to be particularly impaired by ELM [13]. Thus, mentalization-based (MB) interventions foster social cognition in parents and provide an important and at the same time trainable basis on which to improve parents’ capacity to understand the meaning of their child’s behavior, resulting in more adaptive interactions and prevention of maltreatment [14].

A meta-analysis on the effects of parenting programs on child maltreatment prevention encompassing 37 studies provided evidence of positive effects and reduced risk of maltreatment [15]. Via own literature search, we found eleven different prevention programs that aim to enhance mentalizing in mothers with MI [16–21], in prison [22] or at other risk, such as teenage mothers [23], as well as in families [24, 25] and in caregivers of inpatient psychiatric children [26]. The efficacy of four of these approaches that aim to prevent abuse by improving mentalizing in parents has been demonstrated in six randomized-controlled trials (RCTs) [16, 21, 22, 25, 27, 28], and a further two RCTs are currently underway [26, 29]. Previous studies show that mentalization-based (MB) approaches can be delivered by nurses and social workers (e.g., [23]). A meta-analysis [30] including 10 studies encompassing 1628 mother-child dyads with 0–6-year-old children examined the effectiveness of interventions that aimed at promoting maternal sensitivity and reflective functioning. It found that interventions for high-risk families produced the most beneficial effects, with large effect sizes (*d* = 1.5). The authors pointed out that studies should include children in addition to infants and should extend measurements of child outcomes. In sum, data provide evidence for the efficacy of MB approaches in preventing parents from abusing their children, whether they are delivered for individuals, families, or in groups. Previous studies have focused on mothers or parent-couples, leaving open the question of whether they are also successful with fathers. Even more importantly, although several studies have been performed in inpatient treatment settings for addiction [18, 19], so far, no study has been conducted within general psychiatric hospitals for acutely MI parents with different diagnoses of the whole spectrum of mental disorders (e.g., depression, anxiety disorders, borderline personality disorder, addiction, schizophrenia).

We conceptualized a mentalization based-parenting counseling (MB-PC) to improve social cognition in parents in response to their child. In order to evaluate and optimize therapeutic interventions, it is particularly important to understand the biobehavioral mechanisms that underlie these processes and may, thus, induce, influence or moderate the effectiveness of this intervention. Two possible mechanisms of change regarding parenting are social cognition and dyadic synchrony:

First, both affective and cognitive components of social cognition are required for positive parenting: Affective components of social cognition concern the sharing of the child’s emotion (i.e., empathy) and the feelings of warmth and care (i.e., compassion). Cognitive components of social cognition, commonly conceptualized under the terms mentalizing, theory of mind (ToM), or cognitive perspective taking, comprise inferring and reasoning about the child’s cognitive and affective states (i.e., cognitive and affective ToM) [31]. Compromised social cognition in individuals with mental illness and ELM may be a key factor contributing to poor parenting, which impacts on child well-being and mediates the intergenerational continuity of child maltreatment [32]. To our knowledge, to date, no study has addressed the question of which components of social cognition may specifically mediate effects of mentalization-based parenting interventions.

Second, dyadic synchrony is commonly found in well-adjusted children and their parents and has been associated with favorable developmental outcomes [33, 34]. According to the biobehavioral model of parent-child synchrony [35], dyadic synchrony represents a dynamic regulatory process by which hormonal, physiological, and behavioral cues are exchanged between parent and child during social contact in order to jointly pull each other toward a baseline level characterized by greater stability in the system. In a synchronous relationship, when a child becomes distressed, the caregiver will be able to regulate his/her own feelings of discomfort and adopt a soothing demeanor, helping the child to regain emotional balance [36]. The parental ability to mentalize has been linked to observational measures of dyadic interactional quality such as higher sensitivity and lower hostility [37], and these links have also been found in the context of parental ELM and psychopathology [38, 39]. Biobehavioral synchrony could be affected by MB interventions but to date it has not been studied as a mechanism of change.

Taken together, research up to now shows that parental ELM and MI are associated with poor parenting while poor parenting is a risk factor for child maltreatment. MB interventions for parents have been identified as effective in reducing the maltreatment risk for the next generation while no study so far has addressed a group of acutely MI patients currently treated at general psychiatric hospitals. Furthermore, social cognition and dyadic synchrony are of importance for positive parenting and could be mechanisms of change in MB interventions. The present study therefore aims at investigating the effectiveness of an MB intervention on parenting quality in MI parents and possible biobehavioral mechanisms associated with it. The study is part of the multicenter consortium UBICA II (“Understanding and Breaking the Intergenerational Cycle of Abuse in Families Enrolled in Routine Mental Health and Welfare Services”) situated at three sites (Aachen, Berlin, Heidelberg) and subsuming several studies across Germany, led by the managing site at the Department of General Psychiatry at the University Hospital Heidelberg.

## Objectives {7}

The aim of this trial, which is embedded in the consortium UBICA II, is to investigate ways to break the intergenerational cycle of abuse by preventing abuse or neglect in children of MI parents or other parents at high risk of child maltreatment. To this end, the study will test real-life effectiveness of a short (12 h) mentalization-based parental counseling (MB-PC) program integrated into standard clinical treatment in two psychiatric hospitals in a randomized controlled trial (RCT). The clinical relevance of social cognition and parent-child synchrony as mediators of response to MB-PC will further be investigated in two sub-studies of the RCT.

The primary hypothesis of the RCT is that impaired parenting can be improved more by a 12-h combined individual and group MB-PC program enriched by social counseling as add-on to standard clinical care compared to enhanced standard clinical care (standard clinical care plus psychoeducation on positive parenting (SCC+)). Furthermore, we hypothesize that MB-PC-related behavioral and neural changes in social cognition as well as changes in biobehavioral synchrony will mediate the effects of the MB-PC intervention and that ELM will moderate the effects of MB-PC on social cognition and biobehavioral synchrony.

## Trial design {8}

Cluster-randomized, open-label (partially observer-blind), active-control, parallel group superiority clinical trial, with MB-PC groups of 4–8 patients as clusters and 1:1 allocation ratio for clusters.

## Methods: participants, interventions, and outcomes

### Study setting {9}

The Department of General Psychiatry at the University Hospital Heidelberg has 127 in-patient places, 58 day-clinic places, and 2000 cases per year to whom high-frequent out-patient treatment is offered providing mental health care for all citizens of a medium-sized high-socioeconomic status town. Patients come from the whole spectrum of mental disorders with the exception of detoxification treatment. The Psychiatric University Hospital Charité at St. Hedwig Hospital in Berlin has 156 in-patient places, 66 day-clinic places, and 9700 cases per year to whom high-frequent out-patient treatment is provided. It is situated in a metropolitan region with a rather low socioeconomic status, socially troubled areas, high rates of immigrants and addiction disorders. Notably, in-patient and day treatment is offered to acutely ill patients of moderate up to severe degree of illness in Germany with 94% in Heidelberg and 84% in Berlin having entered treatment deliberately. The mean length of stay in in-patient treatment is 25.6 days in Heidelberg and 18.8 days in Berlin, and 28.1 days in day treatment in Heidelberg and 23.2 days in Berlin.

### Eligibility criteria {10}

All patients with a child between 1.5 and 15 years who are in treatment at the Department of General Psychiatry at the University Hospital Heidelberg or the Psychiatric University Hospital Charité at St. Hedwig Hospital in Berlin and have regular contact to their child will be asked to participate in the study. Participation in a clinical trial requires capacity for informed consent and excludes those patients under compulsory treatment. Further exclusion criteria are those which are incompatible with psychotherapy, that is, IQ < 70, severe cognitive impairment of various etiology, and severe impairment in social competency that is not compatible with group interventions according to clinical judgment (i.e., aggressive behavior that endangers other participants or disruptive behavior making execution of the group impossible; patients are excluded from participation in the study if they are not allowed to take part in other group therapies taking place at the in- and outpatient units due to aggressive or disruptive behaviors). The sub-studies comprise additional inclusion criteria due to hormonal analysis and functional magnetic resonance (fMRI) measurements. Informed assent of children (from the age of 6) is necessary for the assessment of children (self-report questionnaires as outcome measures) and their participation in sub-studies. However, participation of a patient in the main trial without assessment of his/her child is also possible.

### Who will take informed consent? {26a}

Informed consent will be obtained by psychologists and medical doctors (at least Masters’s degree level or equivalent) trained to ensure adherence to the study protocol.

### Additional consent provisions for collection and use of participant data and biological specimens {26b}

Not applicable as informed consent is obtained for the RCT and the two sub-studies separately.

### Interventions

#### Explanation for the choice of comparators {6b}

Being the first RCT to test the effectiveness of this adjusted MB-PC program, we intend to test against enhanced standard clinical care, i.e., “treatment as usual,” which is directed against the MI itself and which is enriched by psychoeducation on parenting competences. The expected effect on parenting practices of such a workshop is very small which is why it is suitable as a control intervention in a first RCT. Treatment of the MI according to standard clinical care can have a positive effect on the parent-child relationship. However, a placebo group without psychiatric treatment (i.e., a waiting list) is ethically not acceptable for patients with a severe MI in need for acute treatment.

##### Control intervention (enhanced standard clinical care, SCC+)

Patients assigned to the control intervention take part in the standard clinical care directed at their MI at the Department of General Psychiatry at the University Hospital Heidelberg or at the Psychiatric University Hospital Charité at St. Hedwig Hospital. Additionally, they receive a 90-min workshop on parenting competences not based on mentalization-based therapy. The focus of this workshop is information on positive parenting, parental stress, and stress reduction. Additionally, the workshop entails two exercises on mindfulness. The control intervention is provided by different therapists (social workers and nurses) than the MB-PC.

#### Criteria for discontinuing or modifying allocated interventions {11b}

Before each individual session, patients will be asked about acute suicidality and significant deterioration of psychopathology attributed to the specific study intervention (see also the “Adverse event reporting and harms {22}” section) in which case a medical doctor of the participating hospitals will be informed to ensure treatment of acute suicidality and it will be decided whether participation in MB-PC will be stopped or the session will be postponed. Acute severe somatic illness that makes transfer to another medical department necessary is a further stopping reason.

#### Strategies to improve adherence to interventions {11c}

Therapist adherence to treatment manual will be ensured by regular supervision and will be controlled for by external coders on a random basis using the Revised Adherence Rating Scale [43] that is adapted to MB-PC, with all sessions being videotaped.

For patients, the intervention is part of their routine treatment schedule at the hospital.

#### Relevant concomitant care permitted or prohibited during the trial {11d}

Standard clinical care, i.e., “treatment as usual,” which is directed against the MI itself is provided and, thus, permitted during the trial. Standard clinical care subsumes pharmacotherapy, individual and group psychotherapy focusing on the given disorder, and supplementary creative and sports therapies.

#### Provisions for post-trial care {30}

Not applicable as the trial includes participants who are currently in treatment at a psychiatric hospital.

### Outcomes {12}

#### Primary outcome measure

The primary endpoint of the RCT is parenting practices measured with the Alabama Parenting Questionnaire (validated German version) [44] at follow-up 14 weeks after the end of intervention (T2, see Fig. 1 and Table 1). A slightly modified version will be used for parents of children between 1.5 and 6 years in which items suitable only for older children are either rephrased (e.g., instead of “You ask your child about his/her day at school,” the modified item is “You ask your child about his/her day at kindergarten.”) or left out as missing values as they could not be rephrased accordingly (e.g., “Your child stays out in the evening past the time he/she is supposed to be home”). In all, of the total of 42 items, 15 items had to be rephrased and four items were omitted in the modified version. The version used for parents of children between 1.5 and 6 years in this study will be validated. The APQ will be administered at T0 (pre-intervention), T1 (post-intervention), and T2 (14 weeks after end of intervention) and is a reliable and valid 42 item self-report scale which measures parenting practices across five domains: parental involvement, positive parenting, poor monitoring/supervision, inconsistent discipline, and corporal punishment. It, thus, incorporates characteristics of parenting behaviors which are relevant for child development and conduct rather than emotional climate in the home and has been used as outcome measurement in several RCTs on parenting support programs (e.g., [45, 46]).

**Fig. 1 Fig1:**
[figure not shown]
Trial flow

**Table 1 Tab1:** Overview of the assessments at the different time points

Assessment	Study enrollment	Timepoint study period		
		T0 (pre-intervention)	T1 (post-intervention)	T2 (14 weeks after end of intervention)
Eligibility screen	x			
Informed consent patient and assent child	x			
Primary outcome measure Alabama Parenting Questionnaire (APQ)		x	x	x
Secondary outcome measures (self-report questionnaires on parental stress, parental abuse potential, parental mentalizing capacity, child psychopathology, and child well-being)		x		x
Other measures (diagnostic interviews and self-report questionnaires)		x		
Social cognition paradigms patients (behavioral and fMRI)		x	x	
Social cognition paradigms children 3years and older		x		x
Biobehavioral synchrony paradigm		x		x

#### Secondary outcome measures

Self-report questionnaires will be used to assess the secondary endpoints of the RCT, namely, parental stress (Parental Stress Index, PSI [47]), parental abuse potential (Child Abuse Potential Inventory, CAPI [48]), parental mentalizing capacity (Parental Reflective Functioning Questionnaire [49]), parenting and child rearing attitudes (Adult Adolescent Parenting Inventory, AAPI-2 [50]), parental emotion regulation (Difficulties in Emotion Regulation Scale, DERS [51]), and empathy (Interpersonal Reactivity Index, IRI [52]), all at T2. Additionally, child psychopathology (depending on the age of the child; 18–71 months: Child Behavior Checklist 1,5-5; starting from school enrollment: CBCL 6-18R [53]) and child well-being (KINDL [54, 55]) will be assessed at T2. Children will be asked to evaluate the parenting practices of mother and father using the APQ child version (from age 6), their well-being using the KINDL (from age 4) and their psychopathology using the Youth Self-Report Form (from age 11) [56]. Additionally, the parental APQ will be assessed as a secondary endpoint at end of intervention (T1, see Fig. 1 and Table 1), too.

Outcome measures sub-study a: On the behavioral level, outcome measures comprise behavioral indices for empathy, compassion, affect recognition, and ToM. On the neuronal level outcome measures include neuronal activities of the mentalizing and empathy networks (especially of the medial prefrontal cortex, anterior insula, ventral striatum, superior temporal sulcus bilateral temporo-parietal junction, and precuneus).

Outcome measures sub-study b: On the behavioral level, synchrony between parent and child according to the Coding Interactional Behavior-System (CIB [57]) is the outcome measure; physiological outcome measures include correlations between hormonal levels and heart rate variability of parent and child.

### Participant timeline {13}

At enrollment, patients will be screened for eligibility, and informed consent of the patient and, if applicable, assent of the child will be obtained. Patients can choose whether they take part in the intervention study only or also in one or two of the sub-studies. The intervention starts when a group of 4–8 patients is available which are randomized together to MB-PC or SCC+. Data assessment will take place before the beginning of the intervention (T0), at the end of the intervention (T1) and 14 weeks after end of intervention (T2).

Data assessment of sub-study a takes place at T0 and T1, of sub-study b at T0 and T2. See Table 1 for an overview of the assessments at the different time points.

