Biobehavioral synchrony will be measured within a parent-child interaction paradigm at T0 and T2. This paradigm includes a positive dyadic interaction (i.e., planning a positive joint activity) as well as a stressful dyadic interaction (i.e., solving unsolvable puzzles under time pressure) under controlled laboratory conditions. On the behavioral level, synchrony between parent and child will be measured using the Coding Interactional Behavior-System (CIB; Feldman, 1998). On the biological level, parent-child synchrony of both autonomous nervous system (ANS) activity (i.e., heart rate and heart rate variability) and hormonal release (i.e., cortisol and oxytocin) will be assessed. Study b further administers behavioral tasks on social cognition (empathy, compassion, affect recognition, and ToM) adapted to the age of the child. Children from 3 to 6 years of age will first be presented selected tasks from the Strange Stories task battery [80] and the Extended Theory-of-Mind Scale [81] and the complete Test of Emotion Comprehension [82] to assess ToM. Second, the “Affect Recognition” scale from the NePsy (“A Developmental NEuroPSYchological Assessment” [83]) will be administered. To assess empathy in preschool children, parents will be asked to complete the Empathy Questionnaire (EmQue [84]). Children from 7 to 15 years of age will first perform an almost identical version of the photo-task described above (parental assessment) to study empathy and compassion. Second, to assess ToM-selected tasks from the Strange Stories task battery [80] and a range of advanced ToM tasks will be administered [85]. Third, an almost identical version of the morphing task as described above (parental assessment) to study affect recognition [75] with age adapted instructions will be presented.

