### Methods for additional analyses (e.g., subgroup analyses) {20b}

We will perform subgroup analyses in patients with and without ELM for primary and secondary outcomes.

To test the hypothesis that MB-PC-related behavioral and neural changes in social cognition as well as changes in biobehavioral synchrony will mediate the effects of the MB-PC intervention, we will test the indirect effect of MB-PC (proposed predictor) on outcome scores via parental social cognition and via biobehavioral synchrony (proposed mediators), respectively in a multiple mediator analysis using ordinary least squares regressions with bootstrapping.

To test the hypothesis that ELM will moderate the effects of MB-PC on social cognition and biobehavioral synchrony, we will calculate generalized linear (mixed) models with history of ELM (yes/no) and intervention group (MB-PC versus SCC+) as between-subject factors. A positive interaction between the factors intervention and ELM will indicate that MB-PC exerts particularly high effects in parents affected by ELM.

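### Sub-study b measures synchrony only at the outcome visit (T2), so the planned mediation test cannot show that synchrony drives the parenting effect rather than following from it

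*Protocol article*

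**What the plan says.** The Objectives {7} state as a hypothesis that "changes in biobehavioral synchrony will mediate the effects of the MB-PC intervention", alongside changes in social cognition.

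Methods for additional analyses {20b} gives the test: "we will test the indirect effect of MB-PC (proposed predictor) on outcome scores via parental social cognition and via biobehavioral synchrony (proposed mediators"), carried out "in a multiple mediator analysis using ordinary least squares regressions with bootstrapping". The same sentence covers both sub-studies. It does not say at which visit the outcome scores are taken, and it does not mention temporal order or a reverse path.

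The visit schedule is given three times and agrees each time. Participant timeline {13}: "Data assessment of sub-study a takes place at T0 and T1, of sub-study b at T0 and T2". Plans for assessment {18a}: "Biobehavioral synchrony will be measured within a parent-child interaction paradigm at T0 and T2". The synchrony row of Table 1 is marked at T0 and T2 only.

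The primary endpoint is the APQ at T2, 14 weeks after the intervention ends. The APQ is also given at T0 and T1, and the parental APQ at T1 is a secondary endpoint. The other secondary outcomes are at T2; for example, "child well-being (KINDL [54, 55]) will be assessed at T2". Table 1 has no visit after T2.

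**The concern.** A mediation claim has a direction: the intervention changes the mediator, and the mediator then changes the outcome. When the only post-baseline mediator value comes from the same visit as the outcome, the regression of outcome on mediator is a concurrent association, and the model supplies the direction by assumption. Here the opposite direction is plausible, because the parenting practices that the APQ measures may well shape how parent and child behave together in a laboratory task.

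What is at stake is the mechanism conclusion of sub-study b. The Discussion says that knowledge of such mechanisms will be used to improve the intervention and tailor it to parents. A significant indirect effect reported as mediation could steer that work towards synchrony when synchrony is a consequence of better parenting.

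**Working it through.** **Schedule.** No stated figure decides this point, so the check is to set the timings side by side (Table 1 with the Outcomes and Participant timeline sections).

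| Measure | T0 | T1 | T2 |
|---|---|---|---|
| Parental APQ | x | x | x |
| Other secondary questionnaires | x | – | x |
| Patient social cognition (sub-study a) | x | x | – |
| Synchrony (sub-study b) | x | – | x |

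**Possible mediator-outcome pairs after baseline.**
- Social cognition T1, outcome T2: mediator first.
- Synchrony T2, outcome T2: same visit, order not established.
- Synchrony T2, APQ T1: mediator after the outcome.

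Sub-study b offers only the last two. Using T0-to-T2 changes does not help, because both changes span the same interval. A statistical analysis plan cannot repair this either, since it cannot create an earlier synchrony value or a later outcome.

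**Size of the sub-study.** Recruitment {15} gives 73 per site, so 2 × 73 = 146. Sample size {14} names 177 and, respectively, 120 patients as giving more than 80% power for mediation. These figures cannot be reproduced, because the path coefficients are described only as small to medium.

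**Illustration under a purely reverse path.** All coefficients are assumptions, except that the effect on parenting is set to match the d = 0.4 of the sample size section. X is arm (0/1), m0 and y0 are baseline synchrony and parenting, and each e is an independent standard normal error:
- y0 = 0.3·m0 + e
- Parenting at T2: Y = 0.4·X + 0.5·y0 + 0.87·e
- Synchrony at T2: M = 0.5·m0 + β·Y + 0.8·e

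Synchrony has no effect on parenting in this model. The mediation test is then run as if it did:
- a = coefficient of X in the regression of M on X, m0, y0
- b = coefficient of M in the regression of Y on X, m0, y0, M
- indirect effect = a·b, declared significant if the 95% percentile bootstrap interval excludes 0 (300 resamples, 400 simulated trials)

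| n | β = 0.3 | β = 0.5 |
|---|---|---|
| 120 | 11% | 28% |
| 146 | 14% | 28% |

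The Monte Carlo standard error is √(0.11 × 0.89 / 400) = 1.6 percentage points at 11%, and √(0.28 × 0.72 / 400) = 2.2 points at 28%. An independent repeat gave 11% to 12% and 25% to 28%, and under 1% when parenting and synchrony were unconnected. For comparison, a genuine forward path (MB-PC to synchrony 0.4, synchrony to parenting 0.3) was declared in 67% (n = 120) and 79% (n = 146) of trials. The simulation uses one outcome and one mediator and ignores clustering.

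**The case against.** The strongest reply has four parts.

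**The false-positive rate is limited.** A reader might infer that a significant indirect effect is to be expected under the reverse path. The figures do not support that: with the assumed paths, 72% to 89% of reverse-path trials are not significant. What stands is that the rate exceeds 5%.

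**Correct timing does not make sub-study a causal.** A reader might infer that measuring the mediator at T1 would settle the matter, or that a common cause threatens only sub-study b. Neither follows. Only the intervention is randomised, so unmeasured causes of both mediator and outcome can bias both sub-studies. Temporal order is the one respect in which they differ.

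**The T1 APQ carries information.** It precedes T2 synchrony, so it allows an ordered test of the reverse path and an adjustment of the forward path. It would therefore be too absolute to say that the data are silent on direction. But this helps only for the parental APQ, it does not establish mediation, and section {20b} does not mention it.

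**The text is partly cautious, and the analysis is secondary.** The Introduction and Discussion speak of possible mechanisms and mediators, synchrony is already named as an outcome of sub-study b, and the hypothesis is something to be tested. This is fair. Nevertheless, the analysis is not labelled exploratory, a mediation sample size is given for it, and no wording limits a positive result to association.

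**Conclusion.** The point holds for sub-study b. Its only post-baseline synchrony measurement coincides with the T2 outcomes and follows the T1 APQ, and no outcome comes later. The planned indirect-effect test therefore cannot establish the direction stated in the Objectives. This conclusion rests on the schedule alone, which is consistent throughout the protocol.

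The size, about 11% to 28% false declarations of mediation against a nominal 5%, rests on assumed reverse paths of 0.3 to 0.5 and on the simplifications stated above. It is an illustration and not an estimate for this trial.

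The scope is narrow: the mediation result of one sub-study. The primary comparison, sub-study a, the effect of MB-PC on synchrony, and the test of early life maltreatment as a moderator are untouched. A reader might also take 120 as the planned analysis set of sub-study b. The protocol gives it only as a sample size expected to provide sufficient power, and the link to sub-study b is by order of mention.

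**What to change.** Change the Objectives {7} and Methods for additional analyses {20b} as follows.

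1. Reserve temporally ordered mediation for sub-study a, naming T1 social cognition as mediator and the T2 outcome, and acknowledge that mediator-outcome confounding is not excluded.
2. For sub-study b, report the effect of MB-PC on T2 synchrony and the concurrent association of synchrony with the T2 outcomes, described as non-directional.
3. Add the reverse-order model with parenting as the mediator and T2 synchrony as the outcome, including the version that uses the T1 APQ, which is correctly ordered.
4. Add a sensitivity analysis in which the path from T2 synchrony to T2 APQ is adjusted for T1 APQ. Any remaining association still does not prove mediation.

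All of this uses data already in the schedule. The cost is wording, a few additional regressions and a weaker mechanism statement for sub-study b.

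Moving the synchrony session to T1 is not recommended. Recruitment began in 08/2019, so dyads seen at T2 would be mixed with dyads seen at T1. The follow-up value of the sub-study's own outcome would be lost, and the session would be separated from the children's social cognition tasks, which are also at T0 and T2.
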